***Study Measures (see Appendix for details of specific measures)***

| Baseline                                     | During Study                                                           | Ongoing Monthly Surveys           |
|----------------------------------------------|------------------------------------------------------------------------|-----------------------------------|
| UCLA Loneliness Scale           | Yung’s Loneliness and Distress Scale 4x/day               | UCLA Loneliness Scale             |
| PROMIS Social Isolation Scale   | Alber’s Active and Passive Social Media Use Scale 4x/day  | PROMIS Social Isolation Scale     |
| General Social Media Use Scale  | Social Connectedness Questions 4x/day                                  | General Social Media Use Scale    |
| Georgia Student Health Survey 2.0            | Physical Activity via Actigraph continuously for 14 days               | Georgia Student Health Survey 2.0 |
| Everyday Discrimination Scale   | Sleep via Actigraph for 14 days                                        | Everyday Discrimination Scale     |

[figure not shown]

|                                                                                            |                                                                             |                                                                              |
|--------------------------------------------------------------------------------------------|-----------------------------------------------------------------------------|------------------------------------------------------------------------------|
| CYW Adverse Childhood Experiences Questionnaire for Adolescents: Self Report  | Heart rate variability continuously for at least 24 hours and up to 14 days | CYW Adverse Childhood Experiences Questionnaire for Adolescents: Self Report |
| McMaster Family Functioning Scale                                             |                                                                             | McMaster Family Functioning Scale                                            |
| COVID-19 Experiences (COVEX)                                                  |                                                                             | COVID-19 Experiences (COVEX)                                                 |
| Self-reported physical activity                                               |                                                                             | Self-reported physical activity                                              |
| Self-reported dietary patterns                                                |                                                                             | Self-reported dietary patterns                                               |
| Height, weight                                                                             |                                                                             | Height, weight                                                               |
| Blood pressure                                                                             |                                                                             | Blood pressure                                                               |

## 7. Data and Specimen Banking

All data collected from the activity tracker, heart rate monitor, and EMA assessments will be stored until the completion of data analysis, submission of the next grant, and presentation at academic meetings and journals. We anticipate that this will be 21 months from the study start, which includes additional time needed for participants who agree to participate in monthly survey follow-ups for one year. Only study personnel will have access to the data. We will not release the data to other individuals or research groups.

The data to be stored includes survey responses, sleep and activity data, and heart rate data for each participant.

## 8. Sharing of Results with Participants

Participants will be informed during the consent process that the research team will be monitoring their activity tracker, heart rate monitor, and EMA assessments for the purposes of research only and that most findings will not be disclosed. The exception will be for clinically significant arrhythmias detected on the heart rate monitor or for severe depression or anxiety noted during the baseline or follow-up visit. Participants may not opt-out of being contacted if these are noted. Clinically significant arrhythmias that are incidentally found will be reported to the participant, who may elect to share this with his/her physician. Participants with a score in the range of severe depression (PHQ-9 greater than or equal to 15 on the COVEX questionnaire) or anxiety (GAD-7 greater than or equal to 15 on the COVEX questionnaire) during the baseline or follow-up visit will be contacted by the CHOA Adolescent Medicine psychotherapist via telephone. If a participant notes suicidal ideation

## 9. Study Timelines

Participants who *do not* consent to monthly follow-up surveys following initial study participation will be enrolled in the study for a duration of three months. We anticipate study enrollment to take three months and data analysis/manuscript preparation to

[figure not shown]

take an additional three months. The total time to study completion is estimated to be nine months.

Participants who *do* consent to monthly follow-up surveys following initial study participation will be enrolled in the study for a duration of 15 months (three months for initial study duration and 12 additional months for monthly survey follow-up). We anticipate study enrollment to take three months and data analysis/manuscript preparation to take an additional three months. The total time to study completion is estimated to be 21 months.

## **10. Inclusion and Exclusion Criteria**

Adolescents ages 13-18 years presenting for a primary care visit at the CHOA Adolescent Medicine practice will be recruited to participate in the study. The research coordinator will screen for eligible participants using the clinical calendar in the Epic Electronic Medical Record system.

Inclusion criteria are as follows:

- Age 13-18 years
- Presents for a primary care visit at the CHOA Adolescent Medicine practice
- Ability to speak, read, and comprehend English

Exclusion criteria are as follows:

- Younger than 13 years or older than 18 years
- Unable to speak, read, and comprehend English
- Known cognitive impairment
- Pregnant women or women who become pregnant
- Refusal or inability to provide consent

## **11. Vulnerable Populations**

The proposed study involves the vulnerable population of children under the legal age of consent to procedures involved in the research. While the research involves greater than minimal risk to children presented by a monitoring procedure which is not likely to contribute to the well-being of the subject, we will take safeguards to protect the rights and welfare of these individuals. Written parental permission will be obtained for all individuals under the age of 18 years. Permission of one parent is sufficient even if the other parent is alive, known, competent, reasonably available, and shares legal responsibility for the care and custody of the child. Only parents or legal guardians listed in the child's medical record will be able to provide permission. Additionally, we will obtain written assent from all children to ensure they understand the study and agree to participate. Because participants may receive clinical care from the PI, who is a provider at the CHOA Adolescent Medicine practice, the consent and assent process will be carried out by the research coordinator. This will aid in minimizing coercion or undue influence by the PI.

## **12. Local Number of Participants**

[figure not shown]

A total of 20 participants will be recruited for the study. All participants will be recruited from the CHOA Hughes Spalding Adolescent Medicine Practice. Using the social isolation questions found in the screening survey (ATTACHED), we will split participants into two groups for comparison: socially isolated (n=10) vs non-socially isolated (n=10)

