## 2. Objectives

The purpose of this study is to evaluate the feasibility of enrolling adolescents into a prospective cohort study that uses ecological momentary assessment (EMA) and an activity tracker to quantify the effects of social isolation during the COVID-19 pandemic on mental and cardiovascular health. The objective is to collect pilot data on physical health metrics including physical activity, dietary patterns, sleep, and heart rate variability (HRV), along with measurements of social isolation, social connectedness, and

[figure not shown]

loneliness. These data will be used to apply for funding for a larger cohort study of the effects of social isolation on adolescent mental and cardiovascular health.

The specific aims are:

A1: Evaluate the feasibility of a prospective cohort study of social isolation in adolescence that utilizes ecological momentary assessment and activity tracking.

H1. A recruitment rate of 30% and a retention rate of 80% would indicate feasibility for a larger cohort study.

A2: To quantify the effects of social isolation on adolescent physical activity, dietary quality, sleep, and heart rate variability. Compared to adolescents who are less socially isolated, adolescents who are more socially isolated will have:

H2a: Lower physical activity as measured by an activity tracker

H2b: Less healthy diets as measured on by self-report

H2c: Later sleep onset and less consolidated sleep as measured by an activity tracker

H2d: Lower heart rate variability as measured by a heart rate monitor

A3: To identify factors that exacerbate or mitigate the effects of social isolation on adolescents. This exploratory aim will measure factors such as self-reported social connectedness, loneliness, social media use, adverse childhood experiences, peer victimization, discrimination, family cohesion, as well as sociodemographic factors including gender, race, family income, parental education, and neighborhood poverty level.

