HRV has been associated with both mental health and cardiovascular health outcomes. Baseline HRV is reduced in both adolescents and adults with depression and in adolescents with anxiety. Negative social interactions decrease HRV to a similar degree as the Trier Social Stress Task, and social isolation is associated with reduced HRV in adult women. Important developmental differences in HRV in response to stressors may occur. For example, animal models show a greater impact of social isolation on adolescent cardiovascular reactivity as compared to adult rats. In adults with depression, HRV is further blunted after stressful tasks but in adolescents with depression, HRV may actually increase after stressful tasks. Finally, HRV in adolescence is associated with other important lifestyle factors related to cardiovascular health including physical activity and sleep problems such as variable sleep duration and efficiency.

The figure below, from Holt-Lundstead and Smith, describes pathways linking social connection with cardiovascular health through mechanisms such as lifestyle factors, psychological factors, and biomarkers. In this proposal, we propose a feasibility study using ecological momentary assessment (EMA) and an activity tracker to understand the

[figure not shown]

effect of social isolation in real-time on adolescent behaviors/lifestyle, psychological functioning, and biomarkers relevant to cardiovascular health. This proposal is especially relevant now as adolescents are socially isolated to various degrees during the COVID-19 pandemic.

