### **13. Recruitment Methods**

Adolescents ages 13-18 years presenting for a visit (either in-person or telemedicine) at the CHOA Adolescent Medicine practice will be recruited to participate in the study. The research coordinator will screen for eligible participants using the clinical calendar in the Epic Electronic Medical Record system. Eligible participants will be added to the screening log (ATTACHED) and contacted via phone prior to their visit to see if they are interested in learning more about the study at the time of their visit. Unless a patient declines to learn more about the study at their clinical visit, those presenting in-person will be approached in the waiting room of the clinic while waiting for their primary care visit to start. Interested patients will complete the screening questionnaire (ATTACHED) to ensure eligibility. Next, the research coordinator will explain the study in detail and obtain written informed consent/assent. The study overview and informed consent/assent process will take place in a private research room of the clinic. Alternatively participants will have the option to complete the study enrollment and consent/assent with legal e-signature via REDCap if they prefer to leave the clinical environment after their appointment.

Teens presenting via telemedicine will be asked by their physician if they are interested in learning about the study. If so, they will be informed that they will receive a follow-up call by the research coordinator to schedule a time to discuss the study via Zoom. During the scheduled Zoom videoconference, the research coordinator will explain the study in detail and obtain electronic informed consent/assent with legal e-signature via REDCap.

Participants will be compensated \$25 for their participation in the baseline study visit, up to \$50 for their participation in the home monitoring portion of the study, and \$5 for each future monthly survey completed for a total of up to \$50 for 10 additional surveys. Compensation for participation in the home monitoring portion of the study will be dependent on the number of EMAs completed, proportion of days the activity tracker is worn, and successful return of the monitoring devices. All compensation will be delivered via ClinCard, a reloadable debit card that will be given to the participant at the time of study enrollment. As study procedures are completed, funds will be loaded onto the participants' card.

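### Aim 2 is set up as a 10 vs 10 split on screening questions, although a scored isolation scale is already collected and would use the 20 participants better

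*Protocol*

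**What the plan says.** Section 12 (Local Number of Participants) states that "A total of 20 participants will be recruited for the study". It then fixes the comparison: "we will split participants into two groups for comparison: socially isolated (n=10) vs non-socially isolated (n=10"). Group membership is decided by isolation items in a screening survey. That survey is an attachment that is not part of the text at hand, so its items, scoring and cut-point are unknown.

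Elsewhere isolation is treated as a matter of degree. Section 2 introduces H2a to H2d with "Compared to adolescents who are less socially isolated, adolescents who are more socially isolated will have" lower activity, poorer diet, worse sleep and lower heart rate variability. Section 3 says that "adolescents are socially isolated to various degrees during the COVID-19 pandemic".

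The Study Measures table in section 6 lists the "PROMIS Social Isolation Scale" and the "UCLA Loneliness Scale" at baseline and again in the monthly surveys.

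Section 17 names only within-person tests of baseline against monthly surveys (paired t, Wilcoxon signed-rank, McNemar). It gives no test for the 10 vs 10 comparison and no analysis that uses isolation as a score. It does not exclude one.

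**The concern.** The two-group split is the only between-person comparison that the protocol specifies, so it is the natural reading of how H2a to H2d will be examined. Cutting a graded exposure in two treats adolescents just either side of the cut as opposites and treats all those within a group as alike. In a sample of 20 the lost information matters, and here a scored measure of isolation is collected anyway.

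Aim 2 is secondary to feasibility, but section 2 says these pilot data will support a funding application for a larger cohort. Effect estimates from a coarse exposure would be less precise than they need be.

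**Working it through.** **Inputs.** From the protocol: n = 20 in groups of 10 and 10 (section 12), and significance level 0.05 (section 17), taken as two-sided. Assumed, because the documents do not give them: the distribution of the isolation score, the cut-point, the agreement between the screening questions and PROMIS, and the true correlation between isolation and outcome.

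**The plan's own figure.** There is none for the 10 vs 10 comparison. The power statement in section 17 (at least 80% for a 0.53 SD change) concerns within-person change and does not bear on this point.

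**Information kept by an even cut of a normal score.** With the score standardised, the two halves have means of plus and minus √(2/π) = 0.798. The share of the score's variance that lies between the groups is 0.798² = 2/π = 0.637.
- Loss: 1 − 0.637 = 36%.
- Equivalent sample: 20 × 0.637 = 12.7, so about 13.
- Sample needed with the split to match 20 analysed on the score: 20 / 0.637 = 31.4, so 31 to 32.

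**Power at n = 20.** Simulation with 60,000 replicates and a bivariate normal score and outcome. The score analysis uses t = r√(18/(1 − r²)) on 18 df. The split analysis uses the two-sample t-test on the upper and lower 10.

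| True correlation | Continuous score | 10 vs 10 split |
|---|---|---|
| 0.3 | 25% | 17% |
| 0.5 | 64% | 42% |
| 0.58 | 80% | 56% |
| 0.7 | 96% | 79% |

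So 80% power needs a correlation of about 0.58 with the score and about 0.70 with the split. As a group difference, 10 vs 10 needs 1.32 SD for 80% power.

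**Sensitivity of the 36%.** Each row gives the mean squared correlation between the score and group membership at n = 20.

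| Assumption | Kept | Lost |
|---|---|---|
| Normal score, even cut | 0.64 | 36% |
| Uniform score | 0.72 | 28% |
| Exponential (strongly skewed) score | 0.54 | 46% |
| Screening questions share 70% of variance with the scale | 0.45 | 55% |
| Screening questions share 50% of variance with the scale | 0.33 | 67% |
| 10 lowest and 10 highest of 40 screened | 0.87 | 13% |
| 10 lowest and 10 highest of 67 screened | 0.93 | 7% |

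The uniform and exponential rows are small-sample values. In large samples they become (1/16)/(1/12) = 0.75 and (ln 2)² = 0.48, so losses of 25% and 52%. The two proxy rows are close to 0.7 × 0.637 = 0.45 and 0.5 × 0.637 = 0.32.

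**The case against.** **No fixed loss can be read off this protocol.** The split uses screening questions that are not shown, not PROMIS, and the text nowhere calls it a median split. A reader might infer that the plan discards a third of its information. The documents do not support that as an unconditional statement: the range above runs from 7% to 67%. The low end requires enrolling extremes and passing over the middle, and no section describes such a step.

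**Nothing is thrown away.** The scales are collected, section 17 does not rule out a continuous analysis, and the detail of an exposure model can sit in a statistical analysis plan. This stands in part: the loss can be recovered. But section 12 does state a method, and it is the weaker one.

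**PROMIS may not measure the same thing.** Section 3 defines isolation as a lack of actual connections, while the study cited for the PROMIS scale concerns perceived isolation. This stands as a caveat on the fix. UCLA is further away still: it measures loneliness, which section 3 defines separately.

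**The sample is small either way.** At a correlation of 0.3 neither analysis has useful power (25% and 17%), and the primary objective is feasibility. This stands, and it limits the weight of the point.

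**A quota reading is tempting but unsupported.** Section 13 says "Interested patients will complete the screening questionnaire (ATTACHED) to ensure eligibility", and exact groups of 10 might suggest that willing adolescents are turned away once a group is full, which would lower the recruitment rate. No section says so. Isolation is not an eligibility criterion in section 10, the denominator of the recruitment rate is not defined, and splitting the enrolled 20 at their median gives 10 and 10 with nobody refused.

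**Conclusion.** The point holds in a conditional form. Section 12 commits the Aim 2 comparison to two groups, although the hypotheses are graded and a scored isolation scale is in hand at baseline. If the split acts as a single even cut of a roughly normal score, it loses about 36% of the information, and power at a true correlation of 0.5 falls from 64% to 42%. Other score shapes give about 28 to 46%. An imperfect screening proxy raises the loss to 55 to 67%, and extreme-group enrolment would lower it to 7 to 13%. The direction is the same in every case examined; only the size depends on what is not shown. It affects a secondary aim and does not touch the feasibility endpoints. No effect on the recruitment rate is claimed.

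**What to change.** In section 12 or 17, name the continuous baseline PROMIS Social Isolation score as the main exposure for H2a to H2d, analysed by linear regression or, where the outcome is far from normal, by rank correlation. If the screening questions yield a continuous score and are the preferred measure of isolation, that score can take its place. Keep the 10 vs 10 groups for descriptive tables. If UCLA is analysed, report it as a separate analysis of loneliness and not as a check on the isolation result.

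The cost is wording only: no new data, visits or participant burden. There are two small downsides. Results are expressed per unit of score rather than as a group difference, and PROMIS may not capture exactly what the screening questions do, so the choice between them should be stated with its reason.

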### **13. Recruitment Methods**

Adolescents ages 13-18 years presenting for a visit (either in-person or telemedicine) at the CHOA Adolescent Medicine practice will be recruited to participate in the study. The research coordinator will screen for eligible participants using the clinical calendar in the Epic Electronic Medical Record system. Eligible participants will be added to the screening log (ATTACHED) and contacted via phone prior to their visit to see if they are interested in learning more about the study at the time of their visit. Unless a patient declines to learn more about the study at their clinical visit, those presenting in-person will be approached in the waiting room of the clinic while waiting for their primary care visit to start. Interested patients will complete the screening questionnaire (ATTACHED) to ensure eligibility. Next, the research coordinator will explain the study in detail and obtain written informed consent/assent. The study overview and informed consent/assent process will take place in a private research room of the clinic. Alternatively participants will have the option to complete the study enrollment and consent/assent with legal e-signature via REDCap if they prefer to leave the clinical environment after their appointment.

Teens presenting via telemedicine will be asked by their physician if they are interested in learning about the study. If so, they will be informed that they will receive a follow-up call by the research coordinator to schedule a time to discuss the study via Zoom. During the scheduled Zoom videoconference, the research coordinator will explain the study in detail and obtain electronic informed consent/assent with legal e-signature via REDCap.

Participants will be compensated \$25 for their participation in the baseline study visit, up to \$50 for their participation in the home monitoring portion of the study, and \$5 for each future monthly survey completed for a total of up to \$50 for 10 additional surveys. Compensation for participation in the home monitoring portion of the study will be dependent on the number of EMAs completed, proportion of days the activity tracker is worn, and successful return of the monitoring devices. All compensation will be delivered via ClinCard, a reloadable debit card that will be given to the participant at the time of study enrollment. As study procedures are completed, funds will be loaded onto the participants' card.

